#### Suspension criteria

Serious problems about safety occur in the trial;The curative efficacy of drugs is too poor or even ineffective and has no clinical value in the trial;Severe mistakes of clinical trial protocol are founded that is difficult to evaluate the efficacy of the drug; or obvious deviation occur in the progress of implementation and it is difficult to evaluate efficacy of the drug if it continues;The sponsor requests the suspension (such as financial reasons, management reasons, etc.);The administrative department cancels the test.

### Elimination criteria

Patients do not meet the inclusion criteria are founded after enrollment;Drugs out of prescribed plan are used in the trial;Cases no medication after enrollment;Cases no evaluation or record about medication.

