### Blinding

This is a double-blind (patients and clinicians are blinded) and double-dummy study. A two-stage blind design is adopted. The first stage was the group corresponding to number of each case (such as group A, group B) and the second stage was the intervention corresponding to each group (experimental group or control group).

Treatment assignments will not be revealed until the whole process is completed. Emergency letter will be opened by researchers when emergency (such as severe adverse events) or patient needs rescue and must know the treatment had received. Once the blind is broken, the patient with this number will be withdrawn from the trial handling as a dropout case and the researchers should record the reasons in the case report form (CRF). All emergency letters will be returned together with the CRF after the trial for blind review. When the blind codes are leaked or the opening rate of emergency letter exceeds 20%, the double-blind test will declare failure.

To achieve blinding, the outer packaging of experimental and control drugs should be identical. Size, color, shape, taste, smell and packaging of the simulant are identical to that of the corresponding medicine by adding artificial pigment [23].

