### Exit criteria

Patients will leave the trial when one of the following criteria is met:

The symptoms of patients get worse after 3 days of medication;Some comorbidities, complications or special physiological changes occur during the test;Patients with poor compliance don’t reach 80% of the prescribed amount should be used in the trial;Cases breaking the blind or opening the blind urgently in the trial;Drugs out of prescribed protocol are used in the trial;Patients who want to quit the trial or refuse to accept prescription and examination have the right to withdraw from the trial according to the provisions of the informed consent. And the reason should be understood and documented possibly.

Notice: Whatever reason the cases are dropped out of the trial, the CRF should be kept and transformed into final result using the last result examined, and the efficacy and adverse reactions (ADRs) should be carried out using its full data set.

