### Data statistic and analysis

#### Data selection

Four datasets will be conducted intention to treat (ITT), full analysis sets (FAS), per protocol set (PPS), and safety analysis set (SS). ITT is conducted for efficacy and AEs. FAS refers to the ideal set of participants who are as close as possible to the principle of intention to treat and is obtained after removing the participants from all the randomization with the least and reasonable method. PPS, a subset of FAS, is a data set generated from disease case set fully compliant with the trial protocol. SS refers to the randomized cases that have taken a tested drug at least once with safety evaluation data after treatment.

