### Statistical method

Data analysis will be performed by professional statisticians using SAS 9.1.3. For measurement data, Group t test or Wilcoxon rank sum test will be used for comparison between groups; for counting data, χ^2^ test and Fisher exact test will be used, Rank sum test and Cochran Mantel Haenszel (CMH)test will used for grade data; for efficacy indicators, PPS analysis and FAS analysis will be used at the same time. The statistical analyses will use the two-sided hypothesis test. P ≤ 0.05 will be set as the significant level.

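### The article gives conflicting rules on which children enter the efficacy and safety analyses, so outcome-related exclusions could bias the superiority comparison if they differ between arms

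*Protocol article*

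**What the plan says.** All places are in the protocol article.

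- **Off-protocol drugs.** Exit criteria lists "Drugs out of prescribed protocol are used in the trial" as a reason to leave the trial. Its closing notice says that for every dropout "the CRF should be kept and transformed into final result using the last result examined", and that efficacy and adverse reactions are evaluated on the full data set. Elimination criteria then lists "Drugs out of prescribed plan are used in the trial" beside ineligible, never-medicated and unevaluated cases, and names no analysis set.
- **Efficacy set.** Data selection lists ITT, FAS, PPS and SS as four separate sets and states "ITT is conducted for efficacy and AEs". Statistical method states "for efficacy indicators, PPS analysis and FAS analysis will be used at the same time", and Analysis contents repeats FAS and PPS for effectiveness.
- **Safety set.** The ITT sentence just quoted covers adverse events, yet the same paragraph defines SS for safety.
- **Day-3 failures.** Discontinuation has children without improvement, or with worsening, after 3 days or more switch treatment and stop the study drug. It counts them in PPS as invalid but qualified cases. Exit criteria makes worsening after 3 days a reason to leave. Data selection restricts PPS to cases that complied fully with the protocol.
- **Unblinding.** Blinding allows the emergency letter to be opened for severe adverse events or need for rescue, after which "the patient with this number will be withdrawn from the trial handling as a dropout case". Exit criteria repeats this: "Cases breaking the blind or opening the blind urgently in the trial".

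**The concern.** The trial tests superiority on time to temperature recovery. Taking an off-protocol drug, being unblinded for rescue and failing by day 3 all happen after randomisation, and all are likelier in a child who is still febrile. A rule that deletes such children deletes long recovery times. If the two arms lose them at different rates, the randomised comparison no longer isolates the treatment effect.

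The article gives two answers to whether a child who took an off-protocol drug is analysed, and two answers to which set carries efficacy. A statistician who follows Elimination criteria literally and one who follows the notice under Exit criteria would analyse different children. If the results disagree, nothing in the text says which one decides.

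**Working it through.** **1. The plan's own figures.** The sample size reproduces if the 15.35 h is read as a superiority margin, the ± values as SDs, and power as 80% (not stated). The difference is 46.50 − 30.47 = 16.03 h, and 16.03 − 15.35 = 0.68 h. The pooled variance is (1.74² + 1.69²)/2 = 2.942. Then n = 2 × (1.960 + 0.842)² × 2.942 / 0.68² = 99.9, so 100 per group; 200 × 1.2 = 240. This arithmetic does not bear on the present point, except that the plan itself allows for 20% dropout.

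**2. The passages side by side.**

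| Event | One place | Another place |
|---|---|---|
| Off-protocol drug | Exit criteria: kept in full data set, last result | Elimination criteria: eliminated, set not named |
| Efficacy analysis | Data selection: ITT | Statistical method, Analysis contents: FAS and PPS |
| Adverse events | Data selection: ITT | Data selection: SS defined for safety |
| Day-3 failure who switches | Discontinuation: qualified PPS case | Data selection: PPS fully compliant only; Exit or Elimination criteria may also apply |
| Unblinding | Blinding, Exit criteria: withdrawn as dropout | Exit notice: kept with last result; not in Elimination criteria |

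The first four rows conflict. The fifth does not, but it has a consequence: observation stops, and membership of a fully compliant PPS is probably lost.

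**3. How large a bias could be.** If a fraction p of an arm is removed and the removed children have mean m against an arm mean μ, the arm mean falls by p/(1 − p) × (m − μ). The type I errors below come from simulated two-sample t tests at 0.05 with 120 per arm, a common mean of 46.5 h and no true difference. The SDs and exclusion rates are assumptions. The 12.6 h follows from reading the ± values as standard errors with 54 adults per arm (1.715 × √54), itself an assumption based on the 108-patient adult study mentioned in the Introduction. The 24 h and 25 h are chosen values.

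*Illustration A: normal times, exclusions drawn from the slower half.* Here m − μ = SD × √(2/π) = 0.798 × SD, which is 10.05 h (SD 12.6) or 19.15 h (SD 24).

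- 10% removed in control, 20% in experimental: the factor is 0.2/0.8 − 0.1/0.9 = 0.139. The shift is 1.4 h or 2.7 h in favour of the experimental arm, with type I error about 13%.
- 5% against 20%: the factor is 0.250 − 0.053 = 0.197. The shift is 2.0 h or about 3.7 to 3.8 h, with type I error about 19 to 20%.
- 10% in both arms: no shift, with type I error about 5%.

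*Illustration B: gamma times, SD 25 h, exclusions in one arm only, from children above 72 h.* In this distribution 14.7% lie above 72 h, with a mean of 91.7 h.

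- A quarter of them removed: p = 3.7%. The shift is 0.0367/0.9633 × 45.2 = 1.7 h, with type I error 8.0 to 8.5% across runs.
- Half removed: p = 7.3%. The shift is 0.0734/0.9266 × 45.2 = 3.6 h, with type I error 21 to 22%.
- The same removal in both arms: type I error about 5%.

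**The case against.** The best defence is that exit and elimination answer different questions. Exit ends participation, while elimination concerns analysis sets. If the elimination list is taken as a PPS list, it is compatible with the notice that keeps dropouts in the full data set. That reading is sensible, but the text does not state it. The list also contains ineligible, never-medicated and unevaluated cases, which are items that often define an FAS, and the FAS is described only as the result of minimal, reasonable removals. The ambiguity therefore stands.

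It is also fair to say that naming a primary set is commonly left to an analysis plan, that FAS is described as close to intention to treat, and that running FAS and PPS together may simply mean reporting both. The absence of a named primary set is thus no fault by itself. What remains is that the article assigns efficacy to different sets in different sections.

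Four stronger readings are tempting and are not supported:

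- *Unblinded children are removed from the comparison.* Unblinding is not in the elimination list, and the exit notice keeps these children with the last result. Their loss is later follow-up and probably PPS membership.
- *Day-3 failures are deleted.* Discontinuation has them complete the post-treatment evaluation and counts them in PPS as failures. The difficulty is with the fully compliant definition of PPS, and with the possibility that the switch itself counts as an off-protocol drug.
- *Any febrile child given an antipyretic is eliminated.* Concomitant provides for antipyretics and records their use as a secondary outcome.
- *The plan lets the better of two results be chosen.* No passage says so; the text only fails to say which result decides.

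The simulations are also open to challenge. They assume the SDs, they ignore the last-result rule, and they require unequal exclusion in a double-blind trial. That criticism stands and limits what the figures show.

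**Conclusion.** The point holds as a set of internal contradictions: the fate of children who take off-protocol drugs, the set for efficacy, the set for adverse events, and the PPS status of day-3 failures who switch treatment. These are conflicting statements, not detail deferred to another document.

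The consequence is conditional. Equal exclusions leave type I error near 5%. Unequal, outcome-related exclusions gave roughly 8% to 22% in the illustrations, with mean shifts of 1.4 to 3.8 h. These figures rest on assumed SDs of about 12 to 25 h, assumed exclusion rates of up to 20% in an arm, and complete deletion of the excluded children. They show what literal use of the elimination list could do, and do not predict this trial's error rate. Equal rates cannot be presumed, since the arms receive different drugs, but nothing in the article shows that the rates will differ.

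The unblinding element is the weakest. The child is retained in the full data set, but a carried-forward last result does not show when the temperature of a child still febrile at exit recovered.

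**What to change.** Before the data are unblinded:

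1. Name FAS, analysed as randomised, as the single primary efficacy set for the superiority test, with PPS supportive.
2. State that the off-protocol-drug item in Elimination criteria excludes from PPS only, and align the other items on that list with the FAS definition.
3. Assign adverse events to SS and remove the sentence in Data selection that assigns efficacy and adverse events to ITT.
4. State that the temperature and adverse-event observation already scheduled to 120 h continues after unblinding or early exit, unless consent for it is withdrawn.
5. Reconcile Exit criteria, Elimination criteria, Discontinuation and Data selection on how day-3 failures are counted. This concerns their place in the analysis sets, not how they are treated.

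The cost is mostly wording in the protocol and analysis plan. The one practical burden is that some data collection continues in children who leave treatment, at time points the schedule already contains.

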### Informed consent

The participants are between 2 ~ 14 years old. After a full explanation by the clinicians, written informed consent from participants (or their parent or legal guardian in the case of children under 16) will be obtained before intervention [24, 25].The doctor should describe the purpose, process, and likely risks of this trial in writing to the patient or their guardian before patients enrolled in the trial. Every patient has the right to withdraw from the trial at any time. Written informed consent will be kept in the study file.

### Interventions

All researchers are clinical doctors and they will receive standardized training before starting trial. The experimental drug is RDN and the control drug is Oseltamivir. RDN simulant and Oseltamivir simulant have no active ingredients, the former is intravenous drip with normal saline (NS) or grape sugar (GS) avoiding light and the latter is identical with Oseltamivir’s color, flavor and appearance. The detailed method of administration of two groups is shown in Table 1. And the curative course is five day and each 24 h has an evaluation.

**Table 1 Tab1:** The detailed method of administration of two groups

	Age/Weight	Administration
**RDN and its simulant**	2 ≤ Age ≤ 5 years	0.5ml/kg/day, maximum is no more than 10ml/day 5%GS/0.9%NS diluted 50 ~ 100ml iv drip 30 ~ 40gtt/min q.d.*5
	6 ≤ Age ≤ 10 years	10ml/day 5%GS/0.9%NS diluted 100 ~ 200ml,iv drip, 30 ~ 60gtt/min q.d.*5
	11 ≤ Age ≤ 13 years	15ml/day 5%GS/0.9%NS diluted 200 ~ 250ml,iv drip, 30 ~ 60gtt/min q.d.*5
	Age = 14 years	20ml/day 5%GS/0.9%NS diluted 250ml,iv drip, 30 ~ 60gtt/min q.d.*5
**Oseltamivir and** **its simulant**	Weight ≤ 15 kg	30 mg, p.o. b.i.d.*5
	15<Weight ≤ 23 kg	45 mg, p.o. b.i.d.*5
	23<Weight ≤ 40 kg	60 mg, p.o. b.i.d.*5
	Weight>40 kg	75 mg, p.o. b.i.d.*5

### Discontinuation

Clinical symptoms and signs have no improvement or aggravation compared with those before enrollment after taking the medicine for 3 days or more. That needs to switch to another treatment and stop the medication. After completing the post-treatment evaluation and related laboratory tests, this case is declared over and this patient is recorded in PPS as invalid and qualified case statistics. When the body temperature of patient returns to normal and the symptoms and signs disappear within 5 days, the drug can be stopped. Follow-up visit is conducted after 24 h. If there is no recurrence, it will be counted as a recovered case.

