#### Enhancement of compliance of patients

Researchers will conduct informed consent carefully to ensure subjects understand experimental requirements fully and comply to trial. They should know that the sponsor will provide free trial medication, laboratory examination fees and so on.Using dose counting method monitors subjects compliance. Compliance = actual dosage/prescribed dosage × 100%. Good drug compliance: 80 − 120%; poor drug compliance: less than 80% or more than 120%.Researcher should require subjects to bring all drugs when follow-up and record on CRF. Patients with poor efficacy and compliance will strengthen follow-up.

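### A permitted early stop on recovery can fall below the 80% compliance floor, so per-protocol membership may depend on the outcome

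*Protocol article*

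**What the plan says.** All of the following comes from the protocol article.

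- **Interventions and Table 1:** "the curative course is five day and each 24 h has an evaluation". Table 1 gives RDN once daily for five days and oseltamivir twice daily for five days, so 5 infusions and 10 oral doses.
- **Discontinuation, recovery:** "When the body temperature of patient returns to normal and the symptoms and signs disappear within 5 days, the drug can be stopped". The child is seen again after 24 h, and "If there is no recurrence, it will be counted as a recovered case". No compliance or PPS status is given.
- **Discontinuation, no improvement at three days or more:** treatment is switched, and "this patient is recorded in PPS as invalid and qualified case statistics".
- **Enhancement of compliance of patients:** "Compliance = actual dosage/prescribed dosage × 100" per cent, with "poor drug compliance: less than 80% or more than 120" per cent.
- **Exit criteria:** a patient leaves the trial if compliance does not "reach 80% of the prescribed amount should be used in the trial". The closing notice keeps dropped-out cases in the full data set with the last result carried forward.
- **Data selection:** the PPS is the subset of the FAS that complied fully with the protocol.
- **Statistical method:** efficacy is analysed in the PPS and the FAS in parallel.

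**The concern.** Each rule is reasonable alone, but together they give no consistent status to a child who recovers quickly and stops as the protocol allows. The compliance denominator is the prescribed dosage, and the only prescription stated is the five-day course. Nothing exempts a permitted stop or shortens the denominator for it.

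The primary outcome is time to temperature recovery. If fast recovery leads to an early stop, and an early stop leads to classification as non-compliant, the outcome itself helps decide who is in the PPS. The PPS would then no longer compare randomised groups subject only to protocol adherence. The two arms could also lose different numbers of children, because the plan expects one drug to act faster. Meanwhile treatment failures who stop with the same share of doses are protected by an explicit sentence. Sites would have to decide whether such children have exited, and statisticians whether they belong in the PPS, case by case.

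**Working it through.** **Step 1. Compliance after a permitted stop.** The document prints no figure for this, so there is none to reproduce. With k full treatment days out of 5, compliance = k/5 × 100% (RDN: k of 5 infusions; oseltamivir: 2k of 10 doses).

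- k = 1: 20%
- k = 2: 40%
- k = 3: 60%
- k = 4: 80%, which just meets the floor

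Only stops after three days or fewer fall below 80%, and the shares are the same for both drugs.

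**Step 2. The rules applied literally to two children who both stop after day 3.**

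- Recovered: compliance 60%; below the floor in Exit criteria; not fully compliant under Data selection; counted as recovered, with no PPS rule.
- Not improved: compliance 60%; below the same floor; expressly recorded in the PPS.

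The dose share is identical and the PPS status differs, and what separates them is the outcome.

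**Step 3. Does the typical child reach this situation?** The planning means (Sample size estimation) are 30.47 h for RDN and 46.50 h for oseltamivir, a difference of 16.03 h. The Primary outcome section requires the temperature to stay down for 24 h. Adding 24 h gives 54.47 h and 70.50 h. Both fall before a fourth-day dose due at 72 h, so both would be at about 60%, provided symptoms and signs have also gone.

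**Step 4. Illustration of unequal loss.** Assumptions not in the document: lognormal recovery times; SD 12.6 h in both arms; a child afebrile by 48 h (48 + 24 = 72 h) may stop before the fourth day; a share f of these children does so.

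- σ² = ln(1 + SD²/mean²), μ = ln(mean) − σ²/2, P(T ≤ 48) = Φ((ln 48 − μ)/σ), with ln 48 = 3.871.
- RDN: σ = 0.397, μ = 3.338, P = 0.910.
- Oseltamivir: σ = 0.266, μ = 3.804, P = 0.600.
- f = 25%: 120 × 0.910 × 0.25 = 27 versus 120 × 0.600 × 0.25 = 18.
- f = 50%: 55 versus 36.

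For scale, 120 randomised against 100 required leaves 20 per arm.

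**Step 5. Effect on the PPS estimate.** The full difference is 16.0 h.

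- Lognormal model as above, stoppers a random 25% or 50% of those afebrile by 48 h: PPS difference 16.7 h or 17.2 h, slightly larger than the full difference.
- Normal model, SD 10 to 20 h, every child stopping at confirmed temperature recovery: 3.4 to 4.4 h.
- The same normal model, symptoms clearing 24 h later: 8.8 to 12.0 h.

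The estimate can move either way, depending on who stops.

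**The case against.** **The denominator could be read generously.** After a permitted stop no further dose is due, so the prescribed amount might mean doses due up to that point, and a child who follows Discontinuation has arguably complied. Low compliance is not among the Elimination criteria, and Analysis contents only asks for such cases to be listed. This stands in part: removal from the PPS follows from combining Exit criteria with Data selection, not from an express rule. But the text does not state the generous reading, and the only prescription it gives is five days.

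**The FAS limits the harm.** This stands. The last-result rule keeps exited children in the full data set. A child who stops on recovery has already reached normal temperature and is seen 24 h later, so the primary outcome is largely observed.

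**The numbers rest on assumptions.** This also stands. The SD, the distribution, the symptom lag and the share stopping are not in the document. The planning means come from adults. Stopping is optional and needs symptoms and signs to disappear as well. If children stop at temperature recovery without 24 h confirmation, nearly all in both arms fall below 80% (100% versus 98% under a normal model with SD 12.5 h), and the imbalance is small.

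**Two stronger readings are tempting and unsupported.**

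- A reader might infer that day-3 failures leave the PPS too. Discontinuation expressly keeps them in.
- A reader might infer that the PPS effect all but vanishes. In the lognormal model it falls to 0.2 h only if every child afebrile by 48 h stops and is excluded (109 versus 72 of 120). Even then it runs from 1.2 h to −1.9 h as the SD goes from 8 to 20 h.

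**Conclusion.** The point holds as a conflict between stated rules. A child who stops on recovery after three days or fewer, as Discontinuation permits, has 20% to 60% compliance and, read literally, meets an exit criterion and falls outside the PPS. A non-improver stopping at three days with the same 60% is kept. PPS membership would then depend on the outcome.

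The compliance percentages rest only on the document. Unequal loss between arms is a possibility that follows if one arm recovers faster. The illustrative 27–55 versus 18–36 of 120 depends on the lognormal model, SD 12.6 h, the planning means and a 25–50% stopping share. Neither the size nor the direction of bias in the PPS estimate can be fixed from the document. The damage is confined to the PPS analysis and to follow-up after exit.

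This should be corrected before unblinding, but it does not invalidate the trial's main comparison and ranks below a must-fix defect.

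**What to change.** - In Enhancement of compliance of patients, define prescribed dosage as the doses due up to the protocol-permitted stop, and apply the 80–120% test to that amount. A child who takes every dose until an allowed stop then has 100% compliance whatever the day, and none is lost for this reason in either arm.
- In Exit criteria and Data selection, state that a permitted stop is neither an exit nor a PPS-exclusion reason.
- Reconcile Exit criteria, Interventions with Table 1, Discontinuation, Data selection and the compliance definition with one another. This is a request for consistency only; it favours no clinical stopping rule.

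The cost is a sentence or two in the compliance definition and the PPS rule, with no extra patients, visits or data.
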